## Abstract

**Background:**

Previous studies in pregnancy have not focused in evaluating the effect of walking during pregnancy and prevention of insomnia. Our general objective is to determine the effect of a walking program in preventing the appearance of insomnia in the third trimester of pregnancy, increasing sleep quality and improving quality of life throughout pregnancy.

**Methods:**

Randomized Controlled trial in parallel in healthy sedentary pregnant women (*n* = 265), Walking_Preg Project (WPP), from university hospital in Granada, Spain. At 12th gestational week (GW), they will be invited to participate and randomly assigned to one of the three arms of study: the intervention group I1 (pedometer, goal of 11,000 steps/day), intervention group I2 (pedometer, no goal) and control (no pedometer). Duration of intervention: 13–32 GW. At 12th, 19th and 31st GW the average steps/day will be measured in groups I1 and I2. At 13th, 20th and 32nd GW, Athens Insomnia Scale (AIS), Pittsburgh Sleep Quality Index (PSQI), Adherence to Mediterranean Diet (AMD), physical activity (short IPAQ), quality of life (PSI), and consumption of toxic substances (caffeine, illegal drugs, alcohol and tobacco) will be collected. Student t test or Mann-Whitney U will be used to compare 19th and 31st GW mean of daily steps between I1 and I2 groups. To compare differences between groups in terms of frequency of insomnia/quality of life for each trimester of pregnancy, Pearson’s Chi-square test or Fisher’s exact test will be used. To determine differences in hours of sleep and quality of sleep throughout each trimester of pregnancy, analysis of variance or Friedman test will be used. McNemar-Bowker test will be used to assess differences in life quality in pre-post analyses in the 3 arms. We will use Stata 15 statistical software.

**Discussion:**

promoting walking in second half of pregnancy through use of pedometer and health pre-registration of a goal to be achieved –'10,000–11,000 steps a day’– should prevent appearance of insomnia in third trimester, will increase sleep quality and quality of life in pregnant women.

**Trial registration:**

ClinicalTrials.gov Identifier: NCT03735381. Registered 8th November, 2018.

## Background

The prevalence of insomnia at the beginning of pregnancy is around 40%, reaching over 60% in the third trimester of pregnancy [1–4]. Insomnia is associated with an increase of gestational diabetes mellitus (GDM), depression in pregnancy and postpartum, arterial hypertension and preeclampsia as a result of the increase in cytokine levels derived from sleep deprivation [5]. Insomnia is also involved in unplanned caesarean sections, prolonged labour, premature placental abruption, delayed intrauterine growth and prematurity [6].

It has been documented that practice of physical activity (PA) prevents the onset of insomnia in adults [7], postmenopausal women [8] and pregnant women [9]. In addition, the practice of regular PA (> 150 min/week) also increases the quality of sleep in adults [10] and in pregnancy [11]. However, only 20.3–30% of pregnant women are active [12, 13]. In fact, pregnant women spend more than 50% of their time in sedentary activities [14]. To make an objective assessment of this, a woman who counts less than 5000 steps/day on average could be considered sedentary [15].

Walking is one of the recommended activities in the guidelines of PA in pregnant women in Canada, Japan, Norway and Spain and the most carried out during pregnancy [16, 17]. However, the number of steps/days counted in the first trimester of pregnancy does not exceed 5000 steps [18], which is half of those recommended (10,000-11,000) [19] and decreases as the gestation progresses [18]. Walking during pregnancy regulates, prevents or delays the increase in blood pressure and cholesterol in healthy women [20], decreases the prevalence of type 2 diabetes mellitus [21] and improves glycaemic control of pregnant women with GDM [22]. Moreover, improves cardiorespiratory capacity [23], decreases stress and anxiety and improves sleep quality [24], increases quality of life [25] and reduces weight gain during pregnancy [26].

The pedometer is a cost-effective tool that increases the motivation to walk and increase the number of steps per day by 2000 to 2500 [27] compared to those who do not use it. The effectiveness of the pedometer is greater when establishing a goal to achieve [28]. Different studies carried out in pregnant women show that when all the participants of the study use a pedometer, the establishment of a goal of steps to be reached per day (10,000-11,000) increases the mood and number of steps walked by the person receiving such information [26, 29–33].

Some effects evaluated with the use of pedometers in pregnant women are the increase of mood [34], the decrease in weight gain in obese pregnant women [26, 30], the decrease in the incidence of preeclampsia [35] and the reduction of back pain [36]. However, there are no previous studies that analyse whether an intervention aimed at promoting PA in pregnant women, based on walking, helps to prevent insomnia that appears towards the end of pregnancy and how it could have an impact on the quality of life related to health and sleep quality as pregnancy progresses.

Our hypothesis is that a program to promote walking in the first half of pregnancy through the use of a pedometer and through the health pre-registration of a goal to be achieved –'10,000–11,000 steps a day’– prevents the appearance of insomnia in the third trimester of pregnancy, increases the quality of sleep and improves the quality of life of pregnant women.

### Aim

The main objective of this RCT is to determine the effect of a program aimed at promoting physical activity in pregnant women based on walking during pregnancy in the prevention of sleep hygiene disorders and improvement of the quality of life in the third trimester of pregnancy.

## Methods and design

The Walking_Preg Project, WPP study protocol follows the SPIRIT guidelines and the SPIRIT flow diagram is shown in Fig. 1. Walking_Preg Project (WPP) Consort Flow Diagram is presented in Fig. 2. This is a Randomized Controlled Trial with three groups in parallel: maximum intervention group (I1): with pedometer, information and objective of 10,000 steps/day to be achieved, minimum intervention group (I2), with pedometer and information but without goal of steps to be achieved, and control group (C), without pedometer but with information on physical activity recommendations and their benefits.

**Fig. 1 Fig1:**
[figure not shown]
Walking_Preg Project (WPP) schedule of enrolment, interventions, and assessments

**Fig. 2 Fig2:**
[figure not shown]
Walking_Preg Project (WPP) Consort Flow Diagram

### Arms and interventions

The three groups will receive information about the recommendation of physical activity during pregnancy, according to ACOG guidelines [19].

#### Arm 1

Intervention 1 (I1), maximum intervention: pedometer + goal + reminds (maximum intervention women receive information about the goal of steps/day to be reached: 10,000-11,000. They will receive messages on the mobile phone remembering the goal to achieve and a notification that the researching staff will proceed to collect the average count of steps/day of the week prior to 20th and 32nd GW. Women will get recommendations on physical activity during pregnancy.

#### Arm 2

Intervention 2 (I2), minimum intervention: use of pedometer watch from 12th to 32nd GW (10 weeks). They will not receive goal information nor reminds to collect information from the pedometer. Women will be given recommendations on physical activity during pregnancy.

#### Arm 3

No Intervention, control group: without pedometer. Women will receive recommendations on physical activity during pregnancy.

### Selection criteria for eligibility

Inclusion Criteria: 1) Pregnant women with a minimum of 18 and maximum of 49 years of age; 2) Low medical risk pregnancies that will be attending in the Unit of Obstetrics and Gynecology, in a public third level Maternity Hospital in Granada (Spain); 3) Sedentary women (< 5 days/week of moderate-vigorous physical activity at least > 30 min.; equivalent to < 7000 steps/day); 4) With mobile phone and e-mail; 5) Without intellectual deficits or difficulty to understand the language.

Exclusion Criteria: 1) Chronic disease: diabetes, high-pressure, cardiac or respiratory disease, liver or kidney disease or mobility problems; 2) Women with relative or absolute repose needed; 3) Active women (> 5 days/week of moderate-vigorous physical activity at least > 30 min.; equivalent to > 7000 steps/day); 3) Insomnia at beginning of pregnancy or having drugs for sleep problems.

The study sample will consist of women who, meeting the inclusion criteria, agree to participate, upon request for voluntary collaboration and signing of two documents: 1) Informed consent approved by the Provincial Ethics Committee of Granada and 2) Pedometer loan certificate.

### Location and data collection

The collection of the study sample began in June 2019 in the Obstetrics and Gynecology Department, where the first uterine ultrasound is performed at 12th GW. The Service Management Unit of Obstetrics and Gynecology of the Maternal and Child Hospital –Virgen de las Nieves University Hospital Complex, in Granada– is the centre of care reference in the northern area of Granada, a third level hospital that serves a reference population of 439,035 corresponding to a sector of the Granada Metropolitan District and the Basic Health Zone of Alcalá la Real, Jaén. It has been a reference of the Northeast Health Management Area of Granada.

Walking_Preg Project (WPP) schedule of enrolment, interventions, and assessments is shown in Fig. 1. The health staff will inform each woman of the study by referring them to an adjoining consultation enabled for a member of the research team at the hospital. All women who meet the inclusion criteria and sign the informed consent and loan certificate will be invited to participate in the study to reach target sample size. During the pregnancy, three interviews will be conducted by training staff (12th, 20th and 32nd GW), collecting the information in an access database. The period of recruitment of pregnant women will end in December 2020. We have stopped the recruitment from March to August 2020, because of Covid-19. The period of follow-up of women in the study will take place from the time of recruitment of women (12th GW) until delivery.

### Sample size

First, we have carried out the theoretical calculation of the sample size for the definitive study (*n* = 265), based on the following premises: 1) Three study arms: *maximum intervention group*, pedometer + goal + recall (I1): minimum absolute reduction in the prevalence of low compliance with recommendations that are statistically significant to be detected, that it is 15% with respect to I1*; minimum intervention group*, pedometer (I2): minimum absolute reduction in the prevalence of low compliance with recommendations that are statistically significant to be detected, that is 30% with respect to C; and control group (C), with an estimated prevalence of low compliance with physical activity recommendations of 50% [12, 13]. 2) Alpha error: 5%; 3) Power of the study: 80%; 4) Comparison of I1 vs I2: from the previous premises, 120 women would be needed in each arm; Comparison of I1 vs C: from the previous premises, and taking as reference the 120 women of the I1 arm required for the previous comparison, 25 women in the C arm would be required.

A pilot of the previous design was carried out with 72 women not included in this study: 24 women in each arm of the study, interviewed twice (12th and 20th GW), during the months of February to May 2018. The recruitment period was 3 months. To select a total of 265 women, 1 year and 7 months would be required (considering holiday periods and Covid-19). We estimate 20–30% of losses in second and third interviews (due to neonatal loss or abandonment of the study).

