### Outcome measures

Primary outcome measures in the three arms:

1) ***Prevalence of insomnia*** in third trimester of pregnancy (time frame: 32nd GW) will be evaluated with the Insomnia Athens Scale (IAS) [37], an eight-item scale that assesses the quantity and quality of sleep (first five items) and the diurnal repercussion of insomnia (daytime sleepiness, physical and mental functioning and well-being during the day). Each of the items scores from 0 to 3 (affectation of the item from light to severe). The total score ranges from 0 to 24 points, considering insomnia from a score equal to or greater than 6 points (Sensitivity = 93% and Specificity = 85%) or equal to or greater than 7 points (Sensitivity = 84% and Specificity = 90%).

2) ***Change in mean steps/day*** after intervention in the arms using pedometer register (time frame: 19th and 32nd GW).

Secondary outcome measures in the three arms (time frame: 12th, 19th and 32nd GW): ***Quality of sleep*** of pregnant women measure with the Pittsburgh Questionnaire (PSQI) [38], it assesses the quality of the individual’s sleep during the previous month. It consists of 19 items grouped into seven components: quality, latency, duration, efficiency and sleep disturbances, use of medication for sleep and diurnal dysfunction; each component is scored from 0 to 3, according to a Likert scale in which zero is the absence of the symptom and 3 is its maximum presence. This will result in a score that ranges from 0 to 21 points (the higher score, the worse sleep quality): a PSQI score of > 5 indicates poor sleep quality, with a diagnostic sensitivity of 89.6% and a specificity of 86.5%.

Other pre-specified outcome measures in the three arms:

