Finally, a bivariate mixed-effects logistic regression model will be carried out to determine which variables influence the greater frequency of insomnia, considering the latter quantitatively. To delimit the extent to which the associations that appear are explainable by the effect of the rest of the variables included in the study, a multivariate mixed-effects logistic regression model will be constructed. 95% confidence intervals (CI) will be obtained. All contrasts will be bilateral and statistical significance will be considered when the *p* value is ≤0.05. The data analysis will be carried out by intention to process and by protocol, using the Stata / SE v15.0 statistical package.

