## Discussion

Currently, about 60% of pregnant women have insomnia towards the end of pregnancy [1–4]. This study aims to reduce the prevalence of insomnia in the third trimester of pregnancy by 33% in the pedometer + goal group (maximum intervention) and, on the other hand, to reduce the prevalence of insomnia by 16.6% in the pedometer-only group (minimum intervention), compared to the control group (usual advice without pedometer).

Women in the maximum intervention group are expected to have 33% less insomnia in the third trimester of gestation compared to pregnant women in the control group. Furthermore, in the intervention groups, sleep quality will improve (Pittsburgh score < 5) [38], the frequency of symptoms associated with pregnancy (asthenia, anxiety, cramps) will decrease and the performance of daily life activities (measured with the PSI questionnaire) will improve, compared to the control group.

The intervention requires health professional to explain the use of the pedometer and establish a therapeutic alliance with the pregnant woman to reach a goal. The benefits are expected to be obtained during the project and after its completion: 1) During the project, since the participating women will increase their motivation to walk, due to the use of the pedometer, and will benefit from the inclusion of PA in their daily life, such as decreased sedentary lifestyle and weight control in pregnancy. This will even encourage the practice of walking from their closest social or family bond: 2) In the short term, we will know if the expected potential change has managed to reduce the prevalence of insomnia in the third trimester of pregnancy, by at least 33%.

Direct and indirect costs are expected to be saved: 1) Direct cost in pregnant women enrolled in the study —decreasing sleep-related disorders, increasing quality of sleep, quality of life and general well-being; 2) Indirect costs for the Andalusian Health Service: reduction in the number of visits in Primary Health Care derived from the direct consequences of walking during pregnancy, cost reduction in drugs related to the discomfort of pregnancy. Depression, pregnancy weight control, pregnancy-induced high blood pressure, or back pain will be mitigated by promoting pregnancy walking.

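### The only stated power (80%, n = 265) is for compliance with activity recommendations; insomnia, the first primary outcome, has no stated power, and on the inferred targets it is about 45–49% for I1 vs control before losses

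*Protocol article*

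**What the plan says.** **Sizing (Protocol article, Sample size).** The calculation concerns the "minimum absolute reduction in the prevalence of low compliance with recommendations that are statistically significant to be detected". The control arm enters "with an estimated prevalence of low compliance with physical activity recommendations of 50"%. The two differences are given as "that it is 15% with respect to I1" and "that is 30% with respect to C", and the error rates as "Alpha error: 5%; 3) Power of the study: 80"%. The result is 120 women in I1, 120 in I2 and 25 controls, total 265. Losses of 20–30% are expected, but the total is the plain sum 120 + 120 + 25.

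**Outcomes (Outcome measures).** The first primary outcome is the prevalence of insomnia "in third trimester of pregnancy (time frame: 32nd GW) will be evaluated with the Insomnia Athens Scale (IAS"). The second is change in mean steps per day. The remaining outcomes are sleep quality, quality of life, weight gain, birth weight and gestational week at delivery. Compliance with activity recommendations is not listed.

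**Insomnia target (Discussion).** From about 60% late in pregnancy, the study aims to "reduce the prevalence of insomnia in the third trimester of pregnancy by 33% in the pedometer + goal group" and by 16.6% in the pedometer-only group, each against control.

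**Test (Data analysis).** Insomnia is compared between groups by chi-square or Fisher's exact test. "All contrasts will be bilateral", at a 5% threshold.

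**The concern.** The one power figure in the article belongs to a variable that the trial does not list as an outcome. The second primary outcome does not close the gap: it is a mean change in pedometer counts, not a compliance proportion, and controls wear no pedometer.

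The consequence is greatest in the control arm. Its 25 women were chosen to detect a 30-point difference in compliance, yet the Discussion frames the insomnia aim as a comparison with that arm. If insomnia power is well below 80%, a real one-third reduction could easily give a non-significant result. A reader who carries the 80% over to insomnia could then take that result as evidence that walking does not help.

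**Working it through.** **1. The plan's own figure.** The arms attached to the 15% and 30% differences are garbled: I1 is compared with itself, and the 30% against control is attached to I2. The reading that best fits the later comparisons is C 50%, I2 35%, I1 20%.
- I1 vs I2 (20% vs 35%), two-sided 5%, 80% power, pooled-variance formula: 138 per arm (151 with continuity correction). With 120 per arm, power is 74%.
- I1 vs C (20% vs 50%) with I1 fixed at 120: 21 controls, or 26 with continuity correction. The stated 25 is close to the second.

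No single variant gives both 120 and 25. In any case the figures concern compliance only.

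**2. Inputs for insomnia.**
- Control 60% (Discussion).
- 33% ≈ 20/60, so I1 = 40%. 16.6% ≈ 10/60, so I2 = 50%. These rates are inferred, not printed.
- Arm sizes 120/120/25 (Sample size), or as the blocks of nine (1 C, 4 I1, 4 I2) give them: 265/9 = 29.4 and 4 × 29.4 = 117.8, so 118/118/29.

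**3. Formula.** Power = Φ[(|p1 − p2| − 1.96·s0)/s1], with s0 = √[p̄(1 − p̄)(1/n1 + 1/n2)], s1 = √[p1(1 − p1)/n1 + p2(1 − p2)/n2] and p̄ the weighted mean rate.

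**4. I1 vs C, 40% vs 60%, no losses.**
- 120/25: p̄ = 0.434, s0 = 0.1090, s1 = 0.1077. (0.20 − 0.2136)/0.1077 = −0.126, so power is 45.0%.
- 118/29: p̄ = 0.439, s0 = 0.1029, s1 = 0.1015. (0.20 − 0.2016)/0.1015 = −0.016, so power is 49.4%.
- Exact enumeration: chi-square 46.4% and 50.2%; Fisher 42.7% and 43.7%.

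**5. All comparisons.** Losses are applied as one overall fraction to every arm. Ranges cover both sets of arm sizes.

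| Comparison | No losses | 20% losses | 30% losses |
|---|---|---|---|
| I1 vs C (40% vs 60%) | 45–49% | 37–41% | 33–37% |
| I1 vs I2 (40% vs 50%) | 34% | 28% | 25% |
| I2 vs C (50% vs 60%) | 14–16% | 12–13% | 11–12% |

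The overall three-arm chi-square has 46–48% power before losses.

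**6. Sensitivity, I1 vs C.**
- Absolute reading (60% to 27%): 89–92% before losses, about 76–85% after.
- Lower control rate, same one-third relative reduction, before losses. Control 40% (I1 26.7%): 28% at 120/25, 30% at 118/29. Control 50% (I1 33.3%): 36% and 39%. The 40–50% range is an assumption.

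**7. What the design can detect.** Against 60% at 118/29 before losses, 80% power needs an I1 rate of about 32%, a 28-point difference. At 40% vs 60% the 95% interval for the risk difference is about ±1.96 × 0.1015 = ±20 points, as wide on each side as the target effect.

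**The case against.** **The article is open about its endpoint.** Sample size names low compliance repeatedly and never attaches 80% to insomnia. Activity is also measured at every interview by short IPAQ, and sizing on the behaviour that the intervention targets is a disclosed choice. This stands: a reader might infer that the article claims 80% power for insomnia, and it does not. What remains is that the first primary outcome has no stated power.

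**The 60%-to-40% target is inferred.** Sample size works with explicitly absolute reductions, while the Discussion does not say which kind it means. On an absolute reading, I1 vs C would have adequate power before losses. The relative reading is still the better supported: 33% and 16.6% are 20/60 and 10/60, and the Discussion speaks of a third less insomnia than in controls. It must nevertheless be labelled as an inference.

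**The 60% may not apply to these women.** Eligibility excludes insomnia at the beginning of pregnancy, and the Background puts early prevalence at around 40%. The randomised women may therefore have a lower third-trimester rate than the general figure. This stands as a caveat. With the same relative effect, it lowers power further.

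**No result is promised.** A reader might infer that the Discussion guarantees a reduction of at least 33%. It says that the trial will find out whether such a reduction occurred, and elsewhere uses the language of aims and expectations. The fair criticism is that this is optimistic at the available precision.

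**Confidence intervals are already planned.** Data analysis promises them for means, proportions and the regression models. Intervals for between-arm differences in insomnia are not explicitly among them.

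**Conclusion.** The point holds in this form: the stated power and sample size apply to a variable that is not a listed outcome, and no power is given for insomnia at 32 weeks. With a 60% control rate and the Discussion's reductions read as relative, two-sided 5% power for I1 vs control is about 45–49% before losses and 33–41% after the protocol's own 20–30% losses. The other two pairwise comparisons are weaker: 34% for I1 vs I2 and 14–16% for I2 vs control before losses, about 25–28% and 11–13% after.

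The size of the shortfall rests on two assumptions that the article should settle: that the reductions are relative, and that 60% applies to women without insomnia at baseline. The absence of a power statement for insomnia depends on neither.

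**What to change.** 1. In Sample size, state that 265 women and 80% power refer to activity compliance only, and correct the arms attached to the 15% and 30% differences.
2. Add the power for insomnia at 32 weeks before and after 20–30% losses for the three comparisons. State the assumed control rate, note the exclusion of baseline insomnia, and give the smallest detectable difference (about 60% vs 32% at 118/29 before losses).
3. In the Discussion, say whether 33% and 16.6% are relative or absolute. Present the question of an at-least-33% reduction as one that the trial can only estimate with limited precision.
4. In Data analysis, add between-arm risk differences for insomnia with 95% confidence intervals, so that a non-significant result is not read as no effect.

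The cost is rewording and a less favourable stated power. No extra women are needed. The rewording does not raise the power; it makes the limit visible before the results are known.

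### The 120 women per arm for I1 vs I2 do not follow from the stated premises; on the reading that fits the 25 controls, power is about 74%, not 80%, before losses

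*Protocol article*

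**What the plan says.** The Sample size section plans on the prevalence of low compliance with physical activity recommendations, with 5% alpha and 80% power. Its premises are:

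- Control arm: "with an estimated prevalence of low compliance with physical activity recommendations of 50% [12, 13".
- Under I1, an absolute reduction described as "that it is 15% with respect to I1".
- Under I2, an absolute reduction described as "that is 30% with respect to C".

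It then concludes: "Comparison of I1 vs I2: from the previous premises, 120 women would be needed in each arm". With I1 held at 120, it asks for 25 controls, which gives 120 + 120 + 25 = 265. The same section expects 20–30% losses by the second and third interviews; the 265 is simply the sum of the calculated arm sizes.

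Three other places bear on this. Data analysis fixes the sidedness: "All contrasts will be bilateral and statistical significance will be considered when the". The Background says "only 20.3–30% of pregnant women are active [12, 13", citing the references that the Sample size section cites for its 50%. The eligibility criteria admit "Sedentary women (< 5 days/week of moderate-vigorous physical activity at least > 30 min.; equivalent to < 7000 steps/day" and exclude active women.

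**The concern.** A reduction in I1 with respect to I1 has no meaning, so the three planning prevalences cannot be read off the text as printed. A reader must guess which arms the 15 and 30 points separate, and then see whether any guess returns both 120 and 25.

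I1 vs I2 accounts for 240 of the 265 women. If 120 per arm is too few for the difference the trial says it wants to detect, the stated 80% power for that comparison is wrong. The 50% control rate also sits uneasily beside a Background figure from the same references and beside sedentary-only entry, and this rate feeds both calculations.

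**Working it through.** **Inputs.** Two-sided 5% (z = 1.960), 80% power (z = 0.842), control rate 50%, absolute steps of 15 and 30 points, 120 per intervention arm, 25 controls.

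**Formulas for equal arms**, with p̄ the mean of p1 and p2:

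- Pooled: n = [1.960·√(2p̄(1−p̄)) + 0.842·√(p1(1−p1) + p2(1−p2))]² / (p1−p2)²
- Unpooled: n = 7.849·[p1(1−p1) + p2(1−p2)] / (p1−p2)²

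**Trying to reproduce 120 and 25 together.** Controls are the number needed with I1 fixed at 120.

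| Reading | I1 vs I2 | n per arm, pooled / unpooled | I1 vs C | Controls, pooled / unpooled |
|---|---|---|---|---|
| 30 points is I1 vs C, 15 points is I1 vs I2 | 20% vs 35% | 137.9 / 135.2 | 20% vs 50% | 21 / 25 |
| Literal: I2 = 50 − 30, I1 = 20 − 15 | 5% vs 20% | 75.1 / 72.4 | 5% vs 50% | 5 / 10 |
| 15% and 30% taken as prevalences | 15% vs 30% | 120.5 / 117.7 | 15% vs 50% | 13 / 18 |

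With continuity correction, the first reading gives 151 per arm and 26 controls.

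The 25 follows from the first reading. In the unpooled formula, n_C = 0.25 / (0.09/7.849 − 0.16/120) = 0.25 / (0.011467 − 0.001333) = 24.7, which rounds up to 25. The 120 matches only the third reading, which needs 13 to 18 controls rather than 25. No two-sided reading tried returns the pair. A one-sided, continuity-corrected calculation at 20% vs 35% gives 122 per arm, but Data analysis specifies two-sided tests, and the same variant gives 20 controls.

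**Power for I1 vs I2 at 20% vs 35% (pooled).**

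- 120 per arm: the critical difference is 1.960·√(0.275·0.725·2/120) = 0.1130. The standard error under the alternative is √((0.2275 + 0.16)/120) = 0.0568. Power = Φ((0.15 − 0.1130)/0.0568) = Φ(0.65) ≈ 74%.
- 20% losses, 120 × 0.8 = 96 per arm: Φ((0.15 − 0.1263)/0.0635) ≈ 65%.
- 30% losses, 120 × 0.7 = 84 per arm: Φ((0.15 − 0.1350)/0.0679) ≈ 59%.

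Exact enumeration at 120 per arm gives 74.6% for the chi-square test and 70.0% for Fisher's test.

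**Power for I1 vs C at 20% vs 50%, 120 against 25.** It is 80.5% unpooled and 85.6% pooled, so the stated 80% holds for this comparison before losses.

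**Sensitivity to the control rate.** If 20.3–30% are active, then 70–79.7% are not. Taking low compliance at 70–80% with the same steps puts I2 at 55–65% and I1 at 40–50%. Power for I1 vs I2 at 120 per arm is then 64–65%, and 80% power would need about 170–173 per arm (pooled). After 20% or 30% losses, power in this case is about 55% or 50%.

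**The case against.** The labels are garbled, so the 74% depends on a chosen reading. At 120 per arm, power is about 80% for 15% vs 30% and about 94% for 5% vs 20%. That is true, and 74% must be given as conditional. But neither alternative fits the 25 controls, whereas 20% vs 35% does, so it is the best-supported reading.

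A reader might infer that the 25 controls are also wrong, or that the trial's 80% is really 64–74% throughout. The documents do not support this. The 25 comes out of the unpooled formula, I1 vs C keeps at least 80% power at a 50% control rate before losses on the pooled and unpooled calculations, and the lower figures concern I1 vs I2 only.

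A reader might also infer that the Background contradicts the 50%. That is too strong. The short IPAQ has three levels (low, moderate, active), so women who are not active include those at the moderate level. Controls also receive activity advice, so a planning rate for that arm need not equal a population figure. What stands is that the 50% is unexplained, given the shared references and sedentary-only entry.

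That the authors entered the reductions 15% and 30% as prevalences is a plausible origin of the 120, but it is inference.

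Finally, low compliance is not a primary outcome. The primary outcomes are insomnia prevalence and change in steps, and correcting this paragraph does not establish power for either. This limits the consequence but does not make the printed figure right.

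**Conclusion.** The point holds for I1 vs I2. The premise is misprinted, and 120 per arm does not follow from it under two-sided 5% testing. About 135–138 per arm are needed, and 120 gives about 74% power instead of 80%, or about 59–65% after the losses the protocol itself expects. This rests on C 50%, I2 35% and I1 20%, on the normal approximation, and on equal losses in both arms.

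The 64–65% at a control rate of 70–80% is a sensitivity range. It assumes that low compliance is close to the complement of being active and that the 15- and 30-point steps are unchanged. The 25 controls are not in error at a 50% control rate before losses.

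**What to change.** Rewrite the Sample size paragraph:

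- State one set of three prevalences (C, I2, I1) and use it in both calculations.
- Correct the reduction defined against I1 itself, and say which pair of arms each reduction compares.
- Name the formula.
- Justify the 50% against the 20.3–30% active and the sedentary-only entry, or replace it.
- Keep 265 and, if the intended rates are 50%, 35% and 20%, restate I1 vs I2 power as about 74%, and about 59–65% after the expected losses.
- Give the higher control rate as a sensitivity case (about 64–65% before losses).
- Leave the 25 controls as they are, noting that they apply at a 50% control rate before losses.

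The cost is a corrected paragraph and a lower stated power. No extra women are needed.
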